### Further intervention

Thereafter, each participant will receive pro re nata (PRN) conbercept therapy, with regular monitoring for 12 months, at least 1 month apart for the vitrectomy of the study group and 3 months apart for the first intravitreal injection of the control group. PRN conbercept treatment will be performed if the following criteria are met: (1) existence of recent or persisting cystoid retinal lesions, (2) a decrease of no less than 5 ETDRS letters in BCVA, and (3) an increase of 50 μm or more in CST compared with the best value previously achieved. If high-risk PDR without definite vitreous or preretinal hemorrhage or severe NPDR with high-risk characteristics and reduced visual acuity are present, PRP treatment will be administered. Cataract surgery will also be allowed for cataract that affect vision. PPV will be performed if there exist un-clearing vitreous hemorrhage (1–6 months) and/or tractional retinal detachment. Patients with postoperative ocular hypertension will first receive drug treatment to lower their intraocular pressure. If medication is unable to control persistent high intraocular pressure, they will undergo anti-glaucoma surgery. Other further interventions will be conducted based on the specific circumstances.

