## Introduction

### Background and rationale {6a}

Diabetic macular edema (DME), characterized by the accumulation of exudative fluid in the macula, is the leading cause of vision loss in diabetic patients [1]. With optical coherence tomography (OCT), approximately 5.47% of diabetic patients can be diagnosed with DME [2]. Given the rising prevalence of diabetes [3], DME is becoming an increasingly significant public health concern.

Although the pathogenesis of DME remains unclear, over-expression of vascular endothelial growth factor (VEGF) and over-release of inflammatory cytokines are associated with DME according to recent studies [4]. Focal/grid laser treatment was formerly the gold standard for treating DME, but it could only reduce the chance of moderate vision loss and most patients could not regain lost vision after undergoing this procedure [5]. In contrast, vitreous injection of anti-VEGF has demonstrated greater effectiveness and has become the first-line therapy in treating DME [6]. Conbercept is a 141-kDa engineered fusion protein that has a high affinity for binding all isoforms of VEGF-A, VEGF-B, VEGF-C, and PIGF [7]. Single conbercept intravitreal injection (IVC) can reduce ocular VEGF concentration for more than 60 days [8]. Previous studies have shown the effectiveness and safety of IVC in DME treatment [9–11]. However, a considerable proportion of patients do not react effectively to anti-VEGF agents and often require multiple injections [12]. Refractory or persistent DME refers to eyes that have undergone 4 anti-VEGF injections within 6 months and have a persistent central subfield thickness (CST) of 250 μm or more on OCT scans, as determined by the Diabetic Retinopathy Clinical Research Network (DRCR.net) [13]. After 2 years of monthly injections, over 40% of patients in DRCR protocol I had refractory DME [14], and at least 26% patients in RISE/RIDE study had the same issue [15]. Obviously, refractory DME is not uncommon and typically requires additional treatment, elevating the psychological and economic burden of patients [16]. In addition, repeated injections may lead to degeneration of the remaining healthy retinal nerves, increasing the risk of choroidal capillary circulatory disturbance [17]. As a result, there is a great demand for alternative therapy that can effectively manage DME with lower treatment burden.

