### Criteria for discontinuing or modifying allocated interventions {11b}

If serious adverse events occur or are likely to occur that severely impact vision (such as endophthalmitis, retinal damage, etc.), or if patients are unable to tolerate the intervention due to their physical condition, the intervention will be terminated or modified. The patients will withdraw from the study and receive appropriate treatment measures.

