### Relevant concomitant care permitted or prohibited during the trial {11d}

Treatment other than “Further intervention” will be prohibited, while treatment for the fellow eye and management of systemic diseases will be permitted.

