### Cost-effectiveness analysis

Clinical efficacy will be assessed based on BCVA and CST at the last follow-up and compared to that before operation. Cured: BCVA increased ≥ 15 ETDRS letters, CST decreased ≥ 20%, and no cystoid change is observed; improved: BCVA increased ≥ 5 ETDRS letters, CST decreased ≥ 10%, and no cystoid change is observed; invalid: BCVA and CST have no obvious change or deterioration. Effective rate = [*n* (cured) + *n* (improved)]/*n* (total). Costs include direct, indirect, and hidden costs. The registration fees and related examination fees are considered the same, and indirect or hidden costs such as transportation fees and late work fees are ignored. The treatment and drug costs are included in the direct medical cost, which is calculated according to the treatment and drug charge standard in 2023 of Tianjin Third-Level First-Class Hospital. The incremental cost-effectiveness ratio (ICER) is used as the evaluation index in cost-effectiveness analysis. Cost-effectiveness ratio = treatment cost/effective rate. ICER is the ratio of the difference between the treatment costs of the two groups and the difference between the effective rate of the two groups, indicating the cost of each additional effective patient in the study group versus the control group. The average cost of the two groups of treatments is taken as the willingness to pay. If ICER is less than the willingness to pay, the treatment scheme is cost-effective.

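### The rule for as-needed conbercept requires cysts, a 5-letter loss and a 50 μm thickening together, so persisting edema without worsening has no stated re-treatment trigger in either arm

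*Protocol article*

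**What the plan says.** In the protocol article, *Further intervention* puts every participant on as-needed conbercept after the initial treatment. It starts at least 1 month after vitrectomy in the study group and 3 months after the first injection in the control group. The trigger opens with "PRN conbercept treatment will be performed if the following criteria are met: (1) existence of recent or persisting cystoid retinal lesions". The second and third criteria are linked in the words "2) a decrease of no less than 5 ETDRS letters in BCVA, and (3", and the third is a CST increase of 50 μm or more "compared with the best value previously achieved". No other section restates the rule.

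The same paragraph gives separate indications for laser, cataract surgery, vitrectomy and pressure-lowering treatment, and ends: "Other further interventions will be conducted based on the specific circumstances". *Relevant concomitant care* adds: "Treatment other than “Further intervention” will be prohibited". *Criteria for discontinuing or modifying allocated interventions* deals with another situation: "If serious adverse events occur or are likely to occur that severely impact vision", or intolerance of the intervention.

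**The concern.** Criteria 2 and 3 both describe worsening. An eye that never improves, or improves in part and then plateaus, sits at its best CST value. It fails criterion 3 however much fluid remains. Such eyes are to be expected, since the background says: "Obviously, refractory DME is not uncommon and typically requires additional treatment". An eye with cysts and marked new thickening also fails if its vision has not yet dropped by 5 letters.

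The comparator is meant to be effective anti-VEGF therapy, and the trial tests whether surgery is non-inferior to it. If control eyes with active edema stop at three injections because the rule does not reach them, the comparator may be weaker than intended. Re-treatment is a secondary outcome, and treatment cost enters the cost-effectiveness analysis, so both depend directly on how the rule is read.

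**Working it through.** The question is one of logic, and the plan states no figure for it.

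**Step 1. Truth table.** Let C = cysts present, B = loss of at least 5 letters, T = CST rise of at least 50 μm from the best value. There are 2 × 2 × 2 = 8 combinations.

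| Reading | Combinations that trigger | Cysts, no worsening | Cysts and T, loss under 5 letters |
|---|---|---|---|
| C and B and T (as written) | 1 of 8 | no | no |
| C and (B or T) | 3 of 8 | no | yes |
| any one of C, B, T | 7 of 8 | yes | yes |

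These are counts of logical cases, not shares of patients.

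**Step 2. Two invented eyes.** A control eye at 450 μm falls to 400 μm with cysts after loading and stays there. Its rise from the best value is 400 − 400 = 0 μm, so no injection is triggered. A second eye has cysts, a 100 μm rise and a 4-letter loss. It meets C and T but not B, so again there is no trigger.

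**Step 3. Is 'and' a slip?** The same paragraph writes alternatives where it means them: rescue vitrectomy for hemorrhage and/or detachment, and laser for one retinopathy stage or another. The authors may have intended alternatives, but the text does not say so.

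**Step 4. Effect on BCVA.** Let p and q be the shares of control and vitrectomy eyes left untreated by the rule, and d_C and d_V the letters that treatment would have added in each arm. The difference (vitrectomy minus control) shifts by p·d_C − q·d_V, and a positive shift eases non-inferiority. None of the four inputs is in the documents. With assumed values only:
- p = 0.20, q = 0, d_C = 5: 0.20 × 5 = +1.0 letter.
- p = 0, q = 0.20, d_V = 5: −0.20 × 5 = −1.0 letter.
- p = q = 0.20, d_C = d_V = 5: 1.0 − 1.0 = 0.
- p = q = 0.20, d_C = 5, d_V = 0: 1.0 − 0 = +1.0 letter.

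So the sign is open, and equal shares give no shift only if the benefit per eye is also equal.

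**Step 5. Scale for such a shift.** With the article's SD of 9.5 and 46 per arm, SE = 9.5 × √(2/46) = 1.981. At one-sided 0.05, the level that fits the stated 46 (2 × 9.5² × (1.645 + 0.842)² / 25 rounds up to 45), the largest observed deficit that passes is 5 − 1.645 × 1.981 = 1.74 letters. This assumes the same SD in both arms.

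**The case against.** **A worsening-based trigger, identical in both arms, is a legitimate design choice.** This stands as a matter of principle. But the article does not present it as a deliberate choice to withhold treatment from persistent edema.

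**Persistent edema is not barred from treatment.** A reader might infer that such an eye cannot be re-treated at all. The documents do not support that. Concomitant care prohibits only treatment outside Further intervention, and that section's closing sentence is not confined to complications. What is missing is a stated trigger. Nor do the documents say who decides on re-treatment; they say that surgeons and participants are not blinded. Discretion that differs by arm is therefore a risk, not a demonstrated fact.

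**'Persisting' in criterion 1 is not void.** A reader might see a contradiction there. Cysts that never cleared can coexist with worsening from the best value, and such an eye qualifies. Persistence alone does not.

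**Other sections do not strictly conflict with the rule.** The background sentence concerns refractory disease, defined there as four injections within 6 months with CST of 250 μm or more. It sets no rule for this trial, and the refractory rates cited beside it come from other settings. The cost-effectiveness section requires for both successful grades that "no cystoid change is observed; invalid: BCVA and CST have no obvious change or deterioration". That excludes any eye still cystoid at the last follow-up under every re-treatment rule. Cysts may also clear without an injection, and an injection may not clear them.

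**Treating on any one criterion would go too far.** This stands. It would allow injection for a 5-letter loss without edema, for example from cataract or vitreous hemorrhage, which the same section manages differently.

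**Conclusion.** The concern holds in this form: as written, all three criteria must be met. Persisting edema without worsening, and anatomical recurrence with a loss under 5 letters, have no stated re-treatment trigger in either arm. From the start of the as-needed phase to month 12, such eyes go without criterion-based DME treatment or depend on an open-ended sentence in an open-label trial.

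It is tempting to conclude that the rule biases the trial towards non-inferiority. The documents do not support that. Under-treatment of the comparator is possible, but the rule covers both arms, and neither the share of persistent eyes nor the benefit of further treatment is given. The shifts of −1.0 to +1.0 letter above illustrate assumed inputs; they do not estimate this trial. What rests on the text alone is the logic of the rule and the dependence of the re-treatment and cost outcomes on it. The point should be corrected, but it does not by itself invalidate the design.

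**What to change.** In *Further intervention*, for both arms from the start of the as-needed phase, give conbercept when cystoid edema is present on OCT, whether new or persisting, and at least one of these holds:
- CST still above the 300 μm entry threshold;
- a loss of at least 5 letters attributable to DME;
- a CST rise of at least 50 μm from the best value.

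Adding the 300 μm condition gives 16 combinations. The current rule triggers in 2 of them and the revised rule in 7 (8 with cysts, less the one with no further condition). Both eyes in step 2 are resolved if the second is also read as cystoid edema on OCT. Vision loss without edema no longer leads to an injection.

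Limit the closing sentence to conditions other than DME, and record any other DME-directed treatment of the study eye with date and reason.

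**Cost.** This is a short text change, and the article states that recruitment had not started. The downside is somewhat more injections and drug cost in both arms, which may narrow the treatment-burden difference. Table 1 lists BCVA and OCT after baseline only at months 1, 3, 6 and 12. On those visits the rule can act before the endpoint at months 3 and 6 in controls and months 1, 3 and 6 in the study group. Added injections are then at most 51 × 2 = 102 and 51 × 3 = 153, if every eye qualified every time. Extra visits under the planned regular monitoring would raise this ceiling; without them the benefit is limited too.

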### Criteria for discontinuing or modifying allocated interventions {11b}

If serious adverse events occur or are likely to occur that severely impact vision (such as endophthalmitis, retinal damage, etc.), or if patients are unable to tolerate the intervention due to their physical condition, the intervention will be terminated or modified. The patients will withdraw from the study and receive appropriate treatment measures.

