### Trial design {8}

VVV is a single-center, prospective, parallel-group, non-inferiority, randomized controlled trial. Enrolled patients will be randomly assigned at a 1:1 ratio into the study group (PPV combined with ILM peeling) and control group (IVC), and a follow-up period of 12 months is planned. Interim analyses will not be conducted. Figure 1 depicts the trial design flow chart.

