### Eligibility criteria {10}

The following are the criteria for the inclusion of candidates: (1) ≥ 18 years of age; (2) patients and their families fully understand the research and must sign an informed consent form; (3) diagnosed with type 1 or 2 diabetes mellitus; (4) hemoglobin A1c (HbA1c) levels of < 10% within 3 months; (5) moderate or severe nonproliferative diabetic retinopathy (NPDR) and proliferative diabetic retinopathy (PDR) without vitreous/preretinal hemorrhage [33]; (6) clear media for adequate OCT and OCTA images; (7) treatment-naïve DME diagnosed clinically; (8) CST of > 300 μm; (9) Early Treatment Diabetic Retinopathy Study (ETDRS) BCVA between 24 and 73 letters on the day of randomization; (10) treatment within 12 months of DME diagnosis; (11) no contraindication of vitrectomy or conbercept intravitreal injection. Each participant will only have one eye examined. If both eyes are qualified, the researcher will decide which of the eyes will be included in this study.

Exclusion criteria include the following: (1) any previous DME treatment (i.e., anti-VEGF injections, intravitreal corticosteroid usage, or macular photocoagulation); (2) macular edema caused by other diseases (i.e., age-related macular degeneration, retinal vein occlusion); (3) any previous intraocular surgeries (cataract surgery performed at least three months before study entry will not be exclusionary); (4) vision loss caused by other ocular diseases (i.e., glaucoma, high myopia); (5) a follow-up duration of < 12 months; (6) severe dysfunction of the heart, liver, kidney, lung, or other organs.

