### Outcomes {12}

#### Primary outcome

The primary outcome is the changes in BCVA and CST from baseline to month 12 between the two groups.

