### Sample size {14}

The sample size is estimated by the change of BCVA using PASS 15.0 (PASS 15.0.5 NCSS, LLC, USA). According to a published paper [9], mean BCVA change of IVC from baseline to month 12 was 8.2 ± 9.5 ETDRS letters. The maximum difference of 5 ETDRS letters was chosen for non-inferiority margin between groups. The sample size was calculated based on α level of 0.05 and *β* level of 0.2, N1 = N2 = 46. Then, the ultimate sample size is 102 (51 of each group) assuming a 10% dropout rate.

The non-inferiority margin was chosen because 5 ETDRS letters is considered clinical insignificant in practice. And the sample size is also sufficient for analysis of the change of CST based on previous studies [9, 36] (364 ± 88.6 μm and 200 ± 210 μm for IVC and vitrectomy combined with ILM peeling respectively).

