### Statistical methods

#### Statistical methods for primary and secondary outcomes {20a}

Descriptive statistics will be used to summarize study results and demographic variables. Means and standard deviations will be used to describe the normally distributed data, and medians and interquartile ranges will be used for non-normally distributed data. Categorical variables will be described as percentage and frequency. The two-sample *t*-test or Kruskal–Wallis test will be used to assess continuous variables, while the chi-square test will be used to evaluate categorical variables. A two-sided *p* value of less than 0.05 will be considered statistical significance. Besides, the records of patients with missing data will be deleted to ensure the accuracy of the results. All the data will be analyzed by SPSS 25.0 (Chicago, IL, USA).

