### Methods in analysis to handle protocol non-adherence and any statistical methods to handle missing data {20c}

Missing data will be managed using a combination of the last observation carried forward (LOCF) and multiple imputation (MI) methods. Sensitivity analyses will also be performed to assess the impact of different imputation methods on study results.

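### Patients with vision-threatening serious adverse events, or who cannot tolerate the intervention, are withdrawn from the study, so their month-12 outcomes are not collected and the non-inferiority comparison can be biased

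*Protocol article*

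**What the plan says.** All references are to the protocol article.

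- **Trigger and consequence (Criteria for discontinuing or modifying allocated interventions {11b}).** The trigger opens with "If serious adverse events occur or are likely to occur that severely impact vision (such as endophthalmitis, retinal damage, etc" and also covers patients whose physical condition does not let them tolerate the intervention. The intervention is then terminated or modified, and: "The patients will withdraw from the study and receive appropriate treatment measures". Provisions for post-trial care {30} adds that patients who have withdrawn receive standard clinical care.
- **Endpoint (Primary outcome).** "The primary outcome is the changes in BCVA and CST from baseline to month 12 between the two groups".
- **Design and margin (Trial design {8}, Sample size {14}).** "VVV is a single-center, prospective, parallel-group, non-inferiority, randomized controlled trial". "The maximum difference of 5 ETDRS letters was chosen for non-inferiority margin between groups".
- **Missing data, first rule (Statistical methods {20a}).** "the records of patients with missing data will be deleted to ensure the accuracy of the results".
- **Missing data, second rule ({20c}).** "Missing data will be managed using a combination of the last observation carried forward (LOCF) and multiple imputation (MI) methods". Sensitivity analyses across imputation methods are also promised.
- **Eligibility criteria {10}.** Exclusion 5 reads "a follow-up duration of < 12 months".

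No section says that patients withdrawn under {11b} are still assessed at month 12.

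**The concern.** Section {11b} joins two decisions that should be kept apart: ending or changing the allocated treatment, and ending observation. Once the patient leaves the study, the month-12 BCVA and CST are lost, and they are lost because of a harm that bears directly on BCVA. The missingness is therefore related to the outcome by rule, not by chance.

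Neither missing-data rule repairs this. Deletion takes the patient out of the comparison. LOCF may carry forward a value recorded before the event. Multiple imputation under missing-at-random borrows from eyes that did not have the event. A later analysis plan cannot restore measurements that the protocol tells the site to stop taking.

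This matters more than usual in a non-inferiority comparison of an operation with injections. If severe visual losses drop out unequally, the estimated difference moves and the 5-letter margin no longer protects as intended. If they drop out equally, the spread shrinks and the claim becomes easier to reach. The trigger also includes events that are only thought likely, and surgeons are not masked ({17b}), so withdrawal can depend on knowledge of the arm.

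**Working it through.** **1. The plan's own figure.** Inputs from Sample size {14}: SD 9.5 letters, margin 5, α 0.05, β 0.2. Assuming a true difference of 0 and a one-sided α:

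n per arm = 2 × (1.645 + 0.842)² × 9.5² / 5² = 44.6, so 45 by the normal formula. The noncentral-t calculation gives 46 (power 80.5%), which matches the stated 46. Then 46 × 1.1 = 50.6, so 51 per arm and 102 in total. The sample size reproduces at one-sided 0.05 and is not in question here.

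**2. Shift at the article's own complication rate.** Background and rationale {6a} puts PPV complications at about 1%, similar to the rate for repeated injections. Expected eyes per arm: 0.01 × 51 = 0.5. Assume an affected eye ends at −30 letters and the others gain 8.2 (the IVC mean in {14}), a gap of 38.2:

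- all events in the PPV arm: 0.01 × 38.2 = 0.38 letters
- similar rates in both arms: about 0

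**3. Shift if k of 51 PPV eyes are lost and none under IVC.** With remaining eyes at 8.2 and lost eyes at L, shift = k × (8.2 − L) / 51. The values of k and L are assumptions.

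| k | L (letters) | Shift (letters) | Share of 5-letter margin |
|---|---|---|---|
| 1 | −15 | 23.2/51 = 0.45 | 9% |
| 2 | −30 | 76.4/51 = 1.50 | 30% |
| 3 | −45 | 159.6/51 = 3.13 | 63% |

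**4. False non-inferiority for the middle case.** Here PPV must truly sit at the margin, so the all-patient PPV mean is 8.2 − 5 = 3.2. With two eyes at −30, the other 49 average (51 × 3.2 + 60)/49 = 4.56, a shift of 1.36 letters. The standard error at 46 per arm is 9.5 × √(2/46) = 1.98.

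False-claim rate = 1 − Φ(z − 1.36/1.98):

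- one-sided 0.025: 1 − Φ(1.960 − 0.684) = 10%
- one-sided 0.05: 1 − Φ(1.645 − 0.684) = 17%

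Using the 49 and 51 eyes left (standard error 1.90) gives 11% and 18%.

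**5. Simulation with random event counts.** 30,000 runs, 51 per arm, SD 9.5, one-sided 0.05, affected eyes 30 to 40 letters below the rest, affected eyes removed. Event rates are assumptions.

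| Event rate, PPV v IVC | True difference | Declares non-inferiority, all kept | Affected eyes removed |
|---|---|---|---|
| 2% v 0% | −5 | 5–6% | 9–11% |
| 4% v 1% | −5 | 5–6% | 12–15% |
| 6% v 1% | −5 | 5–6% | 19–27% |
| 1% v 4% | −5 | 4–5% | 1–2% |
| 1% v 1% | −5 | 5% | 5% |
| 4% v 4% | −5 | 5% | 5% |
| 1% v 1% | 0 | 79–81% | 83–84% |
| 4% v 4% | 0 | 66–73% | 82–83% |

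An excess in the PPV arm inflates the error, an excess under IVC reverses it, and equal rates leave the error at 5% while raising the chance of a non-inferiority claim.

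Steps 2 to 5 model removal of the affected eyes. Under LOCF or multiple imputation the shift would depend on which values are carried or borrowed, and the article does not allow that to be computed.

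**The case against.** Several points on the other side are sound.

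- **Direction.** A reader might infer that the rule necessarily favours the surgical arm. The article does not support that. It calls the complication rates similar, and Table 1 schedules PPV once and IVC three times, so a rule about terminating or not tolerating an intervention has more occasions to apply in the control arm. This stands: the direction is conditional.
- **Deletion is not settled.** {20c} prescribes LOCF and multiple imputation, which would keep these patients in the analysis, and LOCF would carry a post-event value if one had been recorded. This stands as far as it goes, but it does not supply an unmeasured month-12 outcome.
- **Exclusion 5.** A reader might infer that patients with short follow-up are removed after randomisation. The criterion sits in an eligibility list that Table 1 screens before allocation, and {14} budgets 10% dropout among the 102. Expected availability is the natural reading, so only the wording is at fault.
- **Hidden harm.** A reader might infer that surgical harms would go unseen. Adverse events are recorded at each visit, severe ones go to the ethics committee within 24 hours ({22}), and a monitoring committee reviews data quarterly ({21a}). The events would be known; what is lost is their later course and their effect on the primary outcome.
- **Scope of the trigger.** Not every sight-threatening problem leads to withdrawal: Further intervention manages vitreous hemorrhage, tractional detachment and uncontrolled pressure without mentioning it. This stands, and it adds to the need for clear wording in {11b}.
- **Size.** Two PPV eyes against none is about 4%, four times the quoted rate. It is a scenario, not an expectation.

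**Conclusion.** The point holds in conditional form. As written, {11b} ends outcome collection because of a severe visual harm or intolerance, and neither of the two conflicting missing-data rules recovers the lost values. That can bias the month-12 comparison in either direction.

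At the article's complication rate of about 1% the expected shift is small: about 0 with similar rates, and about 0.4 letters if every event falls in the PPV arm. With one to three PPV eyes lost and none under IVC it is about 0.4 to 3 letters of the 5-letter margin. In the two-eye case it is about 1.4 to 1.5 letters, with a false non-inferiority rate of about 10% at one-sided 0.025 or 17% at one-sided 0.05. The event counts, the letter losses and the split between arms are assumptions; the article gives none of them.

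The similarity of complication rates cannot be used to dismiss the point, because comparing adverse events between these arms is one of the trial's own secondary objectives. The loss cannot be repaired after follow-up has ended.

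**What to change.** 1. In {11b}, separate stopping or modifying the allocated intervention from leaving the study. Suggested text: patients whose intervention is stopped or modified continue BCVA, OCT and adverse-event assessment at the Table 1 visits through month 12 unless they withdraw consent, and are analysed in the arm to which they were assigned.
2. Reconcile {20a} with {20c} so that one missing-data rule applies and these patients are not deleted.
3. Reword exclusion 5 in {10} as expected availability for 12 months, judged at screening, so that it cannot be applied after randomisation.

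The clinical rule on when to stop or change treatment is untouched. The cost is amendment wording; the visits and assessments are already in Table 1, and the sample size does not change.
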